## Abstract

**Background:**

Pain inhibits rehabilitation. In rehabilitation at medical institutions, the usefulness of virtual reality (VR) has been reported in many cases to alleviate pain. In recent years, the demand for home rehabilitation has increased. Unlike in medical situations, the patients targeted for in-home rehabilitation often have chronic pain due to physical and psychosocial factors, and the environment is not specialized for rehabilitation. However, VR might be effective for in-home rehabilitation settings.

**Objective:**

This study aims to evaluate the feasibility of applying VR to home-visit rehabilitation for homebound patients with chronic pain.

**Methods:**

This study will test the feasibility of VR applied to home-visit rehabilitation for patients with chronic pain. A single-arm pre-post comparison will be conducted to evaluate its feasibility. Screening will be conducted on patients who have given consent to participate in the study, and those who have pain that persists or recurs for more than 3 months and receive home-visit rehabilitation will be enrolled in the study. Baseline measurements will be conducted on study participants before the start of the VR intervention. VR-applied home-visit rehabilitation will be conducted once a week for a total of 10 VR interventions. The primary endpoint is the change in pain from the baseline to the tenth intervention. Pain is a subjective symptom of the study participants and will be subjectively assessed by the Numerical Rating Scale of 11 levels from 0 to 10. Pain as the primary endpoint will be measured at 3-time points per rehabilitation session: before, during, and after the rehabilitation so that changes between time points can be evaluated. Secondary endpoints are heart rate variability, range of motion of the area in the musculoskeletal system where the pain occurs, motivation for rehabilitation, catastrophic thoughts of pain, mood state, quality of life, and interviews. Assessments will be conducted at the baseline, first, fifth, and tenth interventions. After completing the clinical study (10 VR interventions), patients will continue their regular home-visit rehabilitation as usual.

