## Methods

### Overview

A single-arm pre-post comparison will be conducted to evaluate the feasibility. This study protocol has been developed using the findings from our case report on the VR applied to home-visit rehabilitation for hemiplegic shoulder pain in a patient with stroke [25]. In this case, VR was newly applied to a part of the home-visit rehabilitation that the patient had been working on. The VR-applied home-visit rehabilitation was carried out on a weekly basis, and during the intervention period, which was close to a month, the results suggested the chronic pain was continuously relieved compared with before the use of VR.

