### Inclusion Criteria

Patients who meet all of the criteria will be enrolled in the study and the criteria are to (1) have pain that persists or recurs for more than 3 months, (2) receive home-visit rehabilitation, (3) have adequate visual and auditory functions to use the VR equipment, (4) have adequate cognitive and perceptual functions to answer questions measuring subjective symptoms, (5) be at least 20 years of age at the time of consent, and (6) give their free and voluntary written consent to participate in the study, after being fully informed. As the study participants are patients with chronic pain in home care and may have different physical and cognitive ability levels, the following points should be noted; no sensory or cognitive impairment has been diagnosed by the family doctor; the patient is able to see and hear the content with the opportunity to trial the VR before the study begins; and there is a good level of understanding of the research description.

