#### Variables

The primary variable is the change in pain from the baseline (before the VR interventions) to the tenth VR intervention. As pain is a subjective symptom of the study participants, it will be subjectively assessed by the Numerical Rating Scale (NRS) on a scale of 0-10, in which 0 indicates no pain at all and 10 indicates the most intense pain experienced so far [36]. The pain as the primary variable will be measured at 3 time points per rehabilitation session: before, during, and after the rehabilitation so that changes between time points will be evaluated.

Secondary variables are heart rate variability (HRV), range of motion (ROM) in the musculoskeletal system area where the pain occurs, motivation for rehabilitation (Behavioral Regulation in Exercise Questionnaire-2 [BREQ-2]), catastrophic thoughts of pain (PCS [Pain Catastrophizing Scale]), mood state (Profile of Mood State 2 [POMS 2]), and quality of life (Short-Form Health Survey [SF-12]).

HRV represents the ability of the heart to respond to physiological and environmental stimuli. Previous studies have shown the feasibility of HRV as a psychophysiological measurement for reactivity to stress [33]. HRV will be measured at the baseline and each VR intervention and changes from the baseline to the tenth intervention will be assessed.

ROM is the range in which each joint of the body can be physiologically exercised without injury or pain. It is one of the outcomes of rehabilitation and is also used to measure the effectiveness in patients with chronic pain [37,38]. ROM of the musculoskeletal system around where the pain occurs will be measured at the baseline and each VR intervention and changes from the baseline to the tenth intervention will be assessed.

The BREQ-2 is a 19-item scale based on self-determination theory to assess behavioral regulation in exercise. BREQ-2 asks questions relating to why they engage in physical activity and exercise, and their responses are measured on a 5-point Likert-type scale ranging from 1 (not true) to 5 (very true). The scale has 5 subscales measuring 5 types of exercise regulations, that are motivation, external regulation, introjected regulation, identified regulation, and intrinsic regulation [39]. The BREQ-2 will be applied at 4 time points, which consist of baseline, first, fifth, and tenth VR interventions and changes in scores between time points will be assessed.

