The PCS assesses the extent to which participants experience magnification, rumination, and helplessness in response to their pain episodes [40]. The PCS has 13 items, each scored on a 5-point Likert scale from 0 to 4 (0: not at all, 4: all the time). The PCS is reported as a total composite score (range 0-52), with higher scores indicating greater catastrophic thoughts about pain. PCS scores will be measured at 4-time points, which consist of baseline, first, fifth, and tenth VR interventions, and changes in scores between time points will be assessed.

The POMS 2 questionnaire is used to monitor mood changes, particularly participants’ psychological stress. This scale consists of subjective feelings in 6 different mood states (tension, depression, anger, fatigue, confusion, and vigor). A 5-point Likert scale, ranging from 0 (not at all) to 4 (extremely), is used for each item. The higher scores indicate more pronounced emotions [41]. POMS 2 will be applied at 4-time points, which consist, of baseline, first, fifth, and tenth VR interventions, and changes in scores between time points will be assessed.

A 12-Item SF-12 is a health-related quality of life scale [42]. SF-12 consists of multiple questions to measure eight health concepts, that are physical functioning, limiting physical health problems, bodily pain, general health, vitality, social functioning, limiting emotional problems, and mental health. Information from all 12 items is used to construct physical and mental component summary measures [43]. The SF-12 will be applied at 3 time points, that are baseline, the fifth, and tenth VR interventions, and changes in scores between time points will be assessed.

Through interviews with study participants at the tenth intervention, the effects of VR-applied home-visit rehabilitation will be evaluated, including pain alleviation, promotion of motivation, improvement in mood state and pain catastrophic thinking, and patients’ and families’ impressions.

As part of the safety evaluation, the presence and degree of subjective symptoms will be checked using the NRS, which is expressed on an 11-point scale from 0 to 10, for pressure pain at the site where the VR equipment is worn, muscle strain from the neck to the shoulders due to the load of the VR equipment, and discomfort caused by viewing VR images (VR sickness) [35]. The adverse event NRS will be measured at each VR intervention.

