### Conclusion

Future validation studies will consider conducting randomized controlled trials as clinical trials to verify efficacy.

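### The objective is feasibility, but the primary endpoint is pain change in completers, and no quantitative feasibility endpoint or criterion is stated

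*Protocol article*

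**What the plan says.** The abstract's Objective is "This study aims to evaluate the feasibility of applying VR to home-visit rehabilitation for homebound patients with chronic pain", and the Introduction ends on the same aim. The Overview ties the design to it: "A single-arm pre-post comparison will be conducted to evaluate the feasibility".

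The endpoints are of another kind. The abstract has "The primary endpoint is the change in pain from the baseline to the tenth intervention", and the Variables section agrees: "The primary variable is the change in pain from the baseline (before the VR interventions) to the tenth VR intervention". Variables lists HRV, ROM, BREQ-2, PCS, POMS 2 and SF-12 as secondary. The abstract's list of secondary endpoints ends with "motivation for rehabilitation, catastrophic thoughts of pain, mood state, quality of life, and interviews", so it adds the interviews.

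Three other places bear on feasibility:

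- **Interview.** "Through interviews with study participants at the tenth intervention, the effects of VR-applied home-visit rehabilitation will be evaluated". It also covers the impressions of patients and families. Table 1 schedules it at session 10 only.
- **VR symptoms.** Pressure pain, neck-to-shoulder strain and VR sickness are rated 0 to 10 at every VR session, as a safety evaluation.
- **Eligibility.** Among the points to note under Inclusion Criteria is that "the patient is able to see and hear the content with the opportunity to trial the VR before the study begins".

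The Statistical Analysis section includes everyone with at least one VR session, but restricts the primary variable to participants with baseline and all 10 sessions. The Safety Evaluation section removes from the study a participant who develops adverse symptoms such as VR sickness.

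**The concern.** The endpoint that should carry the conclusion answers a different question from the objective. Pain could fall significantly among those who finish while many others give up. It could also stay unchanged in a group that attended every session without difficulty. In neither case does the pain test say whether VR can be delivered in home-visit rehabilitation.

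The restriction to completers makes this worse. Those who stop early are the most informative about feasibility, yet they are left out of the primary analysis and have no scheduled interview. The Discussion itself treats feasibility and effectiveness as two separate open matters, and says that introducing VR to older people needs evaluation. No listed endpoint measures that by a count or proportion.

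**Working it through.** **1. Objective against endpoints.**

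| Feasibility question | Where the article touches it | Status |
|---|---|---|
| Do participants complete the course? | 15% dropout allowance (Sample Size); completer set (Statistical Analysis) | Planning assumption and analysis set, not an endpoint |
| How many sessions are done? | Table 1 schedule | Not an endpoint |
| Do participants stop because of VR symptoms? | Symptom ratings each session; exclusion rule (Safety Evaluation) | Safety evaluation; stopping is not an endpoint |
| Is VR acceptable? | Session-10 interview | Secondary endpoint in the abstract, qualitative, not reached by early stoppers |
| What result counts as feasible? | Nowhere | Not stated |

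**2. The plan's own figure.** The 40 comes from a median of earlier studies whose sizes are not given, so it cannot be reproduced. Only the dropout arithmetic can be checked. If 40 is the number enrolled, 40 × (1 − 0.15) = 34 complete and 6 do not. If 40 were the completer target, enrolment would be 40/0.85 = 47.06, rounded up to 48. Below I assume that 40 start VR.

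**3. Precision of a completion proportion at n = 40.** The Wilson 95% interval is [p + z²/(2n) ± z√(p(1−p)/n + z²/(4n²))] / (1 + z²/n), with z = 1.96.

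For 34/40, p = 0.85:

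- Centre: (0.85 + 0.0480)/1.0960 = 0.819
- Half-width: 1.96 × √(0.0031875 + 0.0006003)/1.0960 = 0.110
- Interval: 70.9% to 92.9% (exact Clopper-Pearson: 70.2% to 94.3%)

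Other outcomes, Wilson:

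| Completing | Estimate | 95% CI |
|---|---|---|
| 28/40 | 70% | 55% to 82% |
| 32/40 | 80% | 65% to 90% |
| 34/40 | 85% | 71% to 93% |
| 36/40 | 90% | 77% to 96% |

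**4. Stopping for VR symptoms.** With 0/40, the upper limit of the exact two-sided 95% interval is 1 − 0.025^(1/40) = 8.8%. With 1/40 the interval is 0.1% to 13.2%, and with 2/40 it is 0.6% to 16.9%.

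**5. Whether the 15% allowance could serve as the criterion.** A rule of at least 85% observed completion needs 34/40. If true completion is exactly 85%, P(X ≥ 34) for a binomial with n = 40 is 0.61, so the rule is missed about 39% of the time.

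For illustration, these are exact rules that rule out a lower completion rate. The rates are my assumptions and are not in the article:

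| Rate to rule out | Needed | One-sided alpha | Power at true 85% |
|---|---|---|---|
| 65% | ≥ 32/40 | 0.030 | 0.86 |
| 70% | ≥ 34/40 | 0.024 | 0.61 |
| 75% | ≥ 35/40 | 0.043 | 0.43 |

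**The case against.** A fair defence is that the article does collect feasibility material. Interviews are a listed secondary endpoint and cover acceptability. Symptoms are rated at every VR session with a researcher present, so those who stop early contribute data until they stop. The Statistical Analysis section defines two sets, and reporting the size of each would yield a completion proportion. Flow and attendance reporting is commonly left to the full protocol or analysis plan. The lack of controls and blinding and the small sample are declared as limitations.

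Most of this stands, and it rules out several stronger readings that a reader might infer:

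- **That there is no feasibility measure at all, or that the trial cannot address its question.** The interviews and symptom ratings contradict the first. Attendance and completion will be observable, so feasibility could be described afterwards. What is missing is a named quantitative endpoint and a criterion.
- **That all acceptability data come from finishers.** This is true of the interview only.
- **That a planned decision on a randomised trial is left unsupported.** The Conclusion says only "Future validation studies will consider conducting randomized controlled trials as clinical trials to verify efficacy".
- **That people who fail the pre-study VR trial go uncounted.** The article does not say so. The abstract and the opening of Recruitment Process place screening after consent, so they could be recorded as screening failures. The later text of Recruitment Process describes assessment before consent, so the order is unclear.

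The defence does not remove the mismatch. Objective and primary endpoint are protocol-level choices. The article states both, so neither condensation nor a separate analysis plan explains the gap.

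**Conclusion.** The point holds in this form: the objective is feasibility, the primary endpoint is pain change in completers of all 10 sessions, and no quantitative feasibility endpoint or criterion is stated. If the plan is followed, the headline is an uncontrolled pain p-value that does not answer the stated question.

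On the plan's own dropout figure, about 6 of 40 (15%) fall outside the primary analysis. The sample size is not the obstacle, since 40 starters would give a completion estimate with a 95% CI of about 71% to 93% at 34/40. These figures assume that 40 start VR and that the 15% allowance is realised; the tables in the working show how they move. The change should be made, because it improves what the trial can conclude at little cost.

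**What to change.** Among all who start at least one VR session (an analysis set that the article already defines), name these as feasibility endpoints:

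1. the proportion completing all 10 VR sessions, with a 95% CI;
2. the number of sessions completed;
3. the proportion stopping for VR symptoms, with a 95% CI.

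Report screening failures and failures of the pre-study VR trial in the flow count, and offer the interview to those who stop early. Base the feasibility conclusion on these endpoints, and report pain change as an effect estimate with a CI. The alternative is to restate the objective as preliminary effect.

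Any feasibility criterion should be chosen and justified by the sponsor, and not taken from the 15% dropout allowance.

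Recruitment began in February 2022 and data collection was ongoing in November 2024. A researcher attends every session, so completion and stopping are already partly known to the team. The change should therefore be dated, made before analysis and labelled as added late; it is not true pre-specification.

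**Cost.** A dated amendment and a short interview for early stoppers. The counts need no new data collection, because a researcher is present at every VR session. The downside is that the headline moves from a pain p-value to feasibility estimates that were not pre-specified at the start.

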**Results:**

Recruitment of participants began on February 22, 2022, and data collection is ongoing as of November 2024. The research results will be published in international peer-reviewed journals and through presentations at national and international conferences.

**Conclusions:**

This study will contribute to the development of novel rehabilitation-based solutions for homebound patients who have had difficulty obtaining adequate relief from chronic pain. Future studies will consider conducting randomized controlled trials as clinical trials to validate the efficacy of VR during home-visit rehabilitation for patients with chronic pain.

**International Registered Report Identifier (IRRID):**

DERR1-10.2196/58734

## Introduction

Chronic pain is defined as pain that persists or recurs for longer than 3 months [1]. It is multifactorial with biological, psychological, and social factors and affects an estimated 20% of people worldwide [2]. Rehabilitation has been shown to be effective in improving not only functional disabilities but also chronic pain [3-5]. However, the increase in exercise-induced pain and the fear of exercise due to pain are challenges that hinder effective rehabilitation [6]. Furthermore, as indicated by the fear-avoidance model of pain [7], the experience of chronic pain caused by physical disabilities and exercise-induced pain associated with rehabilitation can increase anxiety and fear in patients. This leads patients to avoid physical activity, including rehabilitation, and the resulting inactivity and depression lead to a vicious cycle that exacerbates chronic pain.

Many homebound patients have chronic pain and functional disabilities [8]. These patients are often anxious and depressed due to restricted social participation [9]. Homebound patients have psychosocial factors, making it difficult to establish a treatment for chronic pain. As many homebound patients are unable to visit medical institutions, home rehabilitation is important. Unlike medical institutions, patients’ homes are not optimal environments for engaging in effective rehabilitation programs. As a result, patients find it difficult to engage in rehabilitation and are more likely to lose their motivation [10]. Maintaining motivation is more difficult when the home rehabilitation session is prolonged [11]. Home rehabilitation for patients with chronic pain requires an approach that not only relieves pain but also considers psychosocial factors, such as depression, anxiety, and low motivation.

Other chronic pain management measures include pharmacotherapy [12,13], interventional therapy [14], and psychotherapy [15]. However, the use of analgesics can lead to dependence, and, in older people with many underlying medical conditions, there is a risk of multiple drug use leading to adverse symptoms [16]. Furthermore, interventional treatment, which requires regular hospital visits and inpatient care, is burdensome for patients at home. Psychotherapy may also be difficult to manage adequately due to human and time constraints on visits by professional staff [17]. Therefore, there is a need for chronic pain management measures that are nonpharmacological and can be easily implemented at home.

Virtual reality (VR) is a 3D computer-generated simulated environment, which attempts to replicate real-world or imaginary environments and interactions [18]. In recent years, VR has been used in a variety of applications in the medical field, including to alleviate pain and facilitate rehabilitation. Immersion in a simulated virtual environment that produces powerful psychological effects, including relaxation, has been shown to be effective in relieving various types of pain, from acute to chronic [19,20]. VR brings a sense of presence that can be very overpowering and diminish a person’s ability to respond to noxious stimuli and attend to nociceptive neural signals, resulting in less perceived pain [21]. This mechanism is described as a distraction, and any strategy used to modulate pain in VR typically builds on a level of distraction [19]. A rehabilitation program with VR can help patients maintain a positive attitude toward rehabilitation and promote recovery of physical functions [22]. For in-home rehabilitation, a focus on motivation and medical costs for homebound patients has been reported to improve training effectiveness due to motivation [23,24]. However, there is currently insufficient clinical evidence regarding the effects of VR for chronic pain in home-visit rehabilitation. This study aims to evaluate the feasibility of applying VR to home rehabilitation for homebound patients with chronic pain. Alleviation of chronic pain using VR will help facilitate rehabilitation; thereby, rehabilitation will be more effective in improving chronic pain.

## Methods

### Overview

A single-arm pre-post comparison will be conducted to evaluate the feasibility. This study protocol has been developed using the findings from our case report on the VR applied to home-visit rehabilitation for hemiplegic shoulder pain in a patient with stroke [25]. In this case, VR was newly applied to a part of the home-visit rehabilitation that the patient had been working on. The VR-applied home-visit rehabilitation was carried out on a weekly basis, and during the intervention period, which was close to a month, the results suggested the chronic pain was continuously relieved compared with before the use of VR.

### Recruitment Process

The study participants will be recruited from several institutions. Screening will be conducted on patients who give consent to participate in the study, and those who meet the criteria will be enrolled as research participants.

Researchers contact the representative of the home health care agency providing the home rehabilitation service, explain the research outline, and establish a cooperative framework. Each representative picks up patients who meet the criteria. Researchers visit the patients, assess them for compliance with the criteria, and obtain explanations and consent. As the study period coincides with the COVID-19 pandemic, researchers should explain to patients and take the following actions: standard infection control measures should be taken during the researchers’ visit; research equipment should be controlled and disinfected by the researchers; and the possibility of COVID-19 infection in relevant personnel should be considered. If there is a possibility that the person concerned may be infected with COVID-19, the visit should be canceled or postponed.

